
### Participant timeline {13}

See the participant timeline in Fig. 3.

**Fig. 3 Fig3:**
[figure not shown]
Schedule of enrolment, intervention, and assessment for proposed TC intervention study involving those with Parkinson’s disease

### Sample size {14}

The estimated number of participants to achieve the study’s objectives is 40, calculated to attain a 93% statistical power in the difference between two means of the independent variables for testing hypotheses with an alpha level of 5% and a minimal clinical important difference (MCID) of 1.13. This estimation is based on the calculation of the minimal clinical important difference that was determined based on the values obtained in past published studies [13, 26–28]. Considering a 10% of dropout rate of the participants recorded from a previous 24-week TC intervention study for those with PD [13], a 5% dropout rate is expected.

### Recruitment {15}

Participants with PD will be recruited in the city of Ottawa and greater Ottawa area, Ontario. All participation in the TC intervention and PA routine will be on the basis that the first randomly allocated 20 participants will be considered for participation in each group. The recruitment of the participants will be obtained through three sources as follows: (1) referrals from local medical clinics (i.e., physician or neurologist offices); (2) local Parkinson’s support groups that are associated with *Parkinson’s Canada*; and (3) bulletin board, newsletters, or postings in the hospital.

## Assignment of interventions: allocation

### Sequence generation {16a}

Potential participants will be screened on the telephone by a research assistant. Participants who are willing and eligible to participate will be randomly assigned in a 1:1 ratio to TC group or PA group by using a concealed block-randomization procedure, stratified by age and sex.

### Concealment mechanism {16b}

The block randomization design will use permuted block sizes of 4 and 6 with the participant assignments placed in opaque, sealed, and serially numbered envelopes and individualized for each participant.

### Implementation {16c}

The randomization schedule will be generated by the data analyst, who will deliver this document in a sealed envelope to the research assistant responsible for assigning the participants to the two groups.

## Assignment of interventions: blinding

### Participants to be blinded {17a}

Changes in the participants’ gait and postural stability and cognitive performance will be evaluated based on their individual baseline scores. This process will ensure that the effects of the two intervention programs are examined instead of the differences in the individual performance or expectations of the participants. The intention and goals of the study will be fully disclosed at the end of the participants’ intervention period.

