### Trial design {8}

A single-blind randomized control trial will be conducted to compare the effects of a TC program with a physical activity (PA) routine (Fig. 1). The study will be conducted for 12 weeks (3 months), and this period will include a 12-week intervention period with primary and secondary outcomes measured at baseline and at 6 and 12 weeks.

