## TC training group

For the TC group, the first 2 weeks of the program will require the participants to work on some light breathing and simple upper-limb forms. The basic TC forms will be introduced with a focus on becoming comfortable with the flow and rhythm of the movements. Each session will run for 60 min and will be supervised by a TC instructor in a community center. The training will be gradual and range from low to moderate intensity. Participants will warm up for 5–10 min, perform core activities for 40 min, and cool down for 5 min. Three sessions will be offered weekly for 12 weeks; the participants will be asked to attend at least two sessions per week. The third to sixth week of the program will focus on incorporating the upper and lower limb into the routine. These classes will focus on practicing the seven TC forms sequentially. The six remaining weeks of the program will focus on repetitions and performance mastery of the basic seven-form routine. The participants will be allowed to practice TC at home. Any TC that the participant performs in their home or on their own time will be recorded by themselves by using a monitoring form that will be distributed to them and collected weekly. The TC instructor will be present at each of the session to monitor the participants’ progress and to ensure that the movements are being performed correctly.

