## Physical activity group

The PA group will track their level of PA over 12 weeks. During this period, the participants will be required to engage in at least 60 min of regular PA on their own for three times per week. Regular PA may include walking, cleaning, performing chores inside the home, and/or climbing the stairs. No restriction will be made to limit other forms of PA. Individuals in the PA group will be permitted to engage in organized sports and instructor-led class such as boxing and dance to ensure that the participant recruitment process is feasible. An active control group was used for comparisons between the groups who will or will not receive formal TC training and to reflect the daily lifestyle and activities of a typical individual with PD from the community. Similar to the TC group, the participants in this group will be asked to complete an activity log form for monitoring, and this form will be collected weekly to monitor their regular PA levels.

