#### Outcomes {12}

All outcome measures will be conducted by the researchers, blind to group allocation, after 1 week (baseline), 6 weeks (mid-intervention), and 12 weeks (post-intervention). The demographic information of the participants, including age, sex, and clinical information such as stage of PD and medication reported, will be collected from the participants.

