#### 3-D motion capture

Gait performance test: Participants will be asked to walk along the 8-m-long walkway at their self-selected comfortable speed during which their movement will be recorded using 3D motion capture for the analysis of their 3D kinematics and kinetics characteristics of the gait. Walking performance will be used as a baseline condition for comparison with obstacle crossing, because it is a simple task to perform and can provide some indications to the participants’ overall health and functional status. Five successful walking trials will be collected.Obstacle crossing test: Participants will perform obstacle crossing in the laboratory for the analysis of their dynamic postural stability and gait performance. An obstacle composed of two upright upholders and a crossing plank with a height of 20 cm will be placed in the middle of the walkway, where the force platforms are embedded. This plank has been made easily collapsible to keep the participants safe to prevent fall. Five successful obstacle-crossing trials will be collected.

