### Methods for additional analyses (e.g., subgroup analyses) {20b}

No planned subgroup analyses were involved in this study. Gender differences are anticipated to be present, but these differences are not one of the primary outcomes of interest or one of the effects of TC training. We do not anticipate any gender effects to remarkably contribute to the effects of TC training. Efforts were made to ensure that only the effects of TC training are examined, by making the intervention groups comparable, setting a strict age range for the participants’ age, and using the individual’s baseline scores for comparisons with their post-training evaluations. Accordingly, we will strictly examine the potential mechanisms and training effects of TC for symptoms related specifically to PD.

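### Scoring against individual baselines does not exclude participants' expectations, as the protocol says it does: participants know their arm and the trial supplies classes to one arm only

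*Protocol article*

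**What the plan says.** The Trial design section states: "A single-blind randomized control trial will be conducted to compare the effects of a TC program with a physical activity (PA) routine". The Outcomes section identifies the blinded party: "All outcome measures will be conducted by the researchers, blind to group allocation".

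The participant-blinding item (17a) describes no masking of allocation. It offers a scoring rule, "Changes in the participants’ gait and postural stability and cognitive performance will be evaluated based on their individual baseline scores", and draws this conclusion from it: "This process will ensure that the effects of the two intervention programs are examined instead of the differences in the individual performance or expectations". It then adds that the study's aims are disclosed in full only once a participant's intervention period is over.

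The item on additional analyses (20b), in a paragraph mainly about gender and age, makes a similar claim: "Efforts were made to ensure that only the effects of TC training are examined, by making the intervention groups comparable". It also relies on an age restriction and on baseline scores.

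The arms differ in what the trial provides. The Tai Chi arm has supervised 60-minute classes, three offered weekly for 12 weeks: "The TC instructor will be present at each of the session to monitor the participants". The control arm is active on its own: "Regular PA may include walking, cleaning, performing chores inside the home, and/or climbing the stairs". Outside instructor-led classes are allowed for the control arm but are not supplied. Both arms return weekly logs and attend the same three laboratory sessions.

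**The concern.** Item 17a should tell the reader whether participants know their allocation. Instead it says that an analysis step makes expectation irrelevant. That is a statement about what the design achieves, and it is not true of change from baseline.

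What is at stake is attribution. If the sentence stands, a difference between arms could be reported as the effect of Tai Chi training with expectation declared excluded. The contrast would in fact combine the Tai Chi content with knowledge of allocation, instructor attention and group contact. The Discussion also expects the biomechanical comparison of the two groups to explain how Tai Chi training works, so the point bears on the conclusions as well as on the blinding item.

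The most exposed outcomes depend on effort or confidence. Toe and heel clearance over a visible obstacle is a primary outcome. Among the secondary outcomes are gait speed, for which participants "walk along the 8-m-long walkway at their self-selected comfortable speed", single-leg stance held as long as possible, and the Timed Up and Go.

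**Working it through.** **1. The plan's own figure.** The only related figure is the 93% power for 40 participants. With 20 per arm, two-sided 5% and 1.13 read as a standardised difference, the noncentrality is 1.13 × √(20/2) = 3.57 and the t-test power is 93.6%. The figure reproduces and is not in dispute here.

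**2. What baseline comparison removes.** For participant *i* write

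- baseline = personᵢ + error
- follow-up = personᵢ + time + (τ + e) × [Tai Chi arm] + error

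Here τ is the effect of Tai Chi itself and e is the between-arm difference in response to expectation, attention and contact. Subtraction cancels personᵢ, so the between-arm difference in mean change is τ + e. Adjusting for baseline as a covariate does not help either, because e follows allocation and is not a function of the baseline score. The Statistical methods section names group × time analysis of variance with adjustment for age and gender; neither part touches e. This assumes that e arises after the baseline measurement. The Outcomes section dates baseline as after 1 week; any response already present by then would partly cancel.

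**3. Can e be zero by design?** That would need participants masked to allocation or arms matched on contact.

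- *Masking:* one arm attends Tai Chi classes and the other logs its own activity, so participants know their arm. The protocol does not say this outright; it follows from the nature of the arms.
- *Contact supplied by the trial, Tai Chi arm:* at most 3 × 1 h × 12 weeks = 36 h. At two sessions a week, 2 × 1 h × 12 = 24 h. The two figures arise because the Tai Chi training group section asks for at least two sessions a week and the adherence section asks for three; those passages need reconciling.
- *Contact supplied by the trial, control arm:* no classes. Outside classes are optional, so actual instructor contact is unknown and not necessarily zero.

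Neither condition is met.

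**4. Illustration only; the values of e are assumed.** Set τ = 0 and test change at one follow-up with a two-sample t-test, 20 per arm. The standardised shift is e / √(2(1 − ρ)), where ρ is the baseline to follow-up correlation, and the noncentrality is that shift × √10. For e = 0.3 and ρ = 0.5: 0.3 / 1 × 3.162 = 0.95, giving a 15% chance of p < 0.05.

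| Assumed e (SD) | Simulated difference in change (ρ = 0.5) | Chance of p < 0.05, ρ = 0.5 | Chance of p < 0.05, ρ = 0.7 |
|---|---|---|---|
| 0 | 0.00 | 5% | 5% |
| 0.2 | 0.20 | 9% | 13% |
| 0.3 | 0.30 | 15% | 22% |
| 0.5 | 0.50 | 34% | 51% |

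The second column carries the point: the whole of e survives subtraction of baseline. The last two columns depend on e and ρ, which the documents do not give.

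**The case against.** The strongest reply is that this is one over-confident sentence in an otherwise open, pragmatic comparison. Much of that stands.

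- **The protocol does take a participant-side step.** Withholding the study's aims may dampen expectation. It does not hide which arm a person is in, and it does not equalise contact.
- **The sentence could refer to differences that exist before the trial.** On that reading own-baseline scoring is apt. But it sits under participant blinding and names expectations without limiting them to the start of the study, so it will be read as covering expectation during the trial.
- **The comparator is legitimate.** The protocol explains why it chose active people living their usual life. Nothing here requires an attention-matched arm.
- **Measurement is protected.** Blinded assessors and instrumented motion capture limit assessment bias. They do not limit changes in participants' effort or confidence. For COM-COP separation, the other primary outcome, the route from effort to result is less clear.

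A reader might also infer more than the documents support:

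- *That contact was 36 hours against none.* 36 is a maximum, and control participants may attend outside instructor-led classes. What holds is that the trial supplies classes to one arm only.
- *That item 20b claims to have excluded attention effects.* Its context is gender and age, and it does not mention instructor contact. Its wording is too broad, but it is secondary to item 17a.
- *That the trial sets out to test its choice of forms and cannot.* The Objectives note that earlier studies did not report how forms were selected, and the protocol answers by describing its own selection. It states no aim of comparing one selection with another.
- *That the false-positive rate is some particular figure.* The rates above rest wholly on assumed shifts.

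**Conclusion.** The point holds as a correction to a stated property of the design. Change from baseline does not ensure that expectation is excluded, and comparable groups at entry do not ensure that only Tai Chi effects are examined. The contrast the trial can estimate is the whole supervised group programme compared with self-directed activity.

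This rests on two things: participants know their arm, which is unavoidable given what the arms are, and the trial supplies 24 to 36 hours of classes, depending on sessions attended per week, to the Tai Chi arm alone. The size and direction of any expectation or contact effect are not in the documents, so no bias figure can be attached. The arms, the sample size and the planned analysis are unaffected. The text should be corrected because, left as it is, it would support a stronger attribution than the data can carry.

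**What to change.** 1. In item 17a, delete the sentence claiming that the process excludes expectations. State that participants are not blinded to allocation and that single-blind refers to the outcome assessors. Keep the statement on late disclosure of the study's aims and describe it as a partial measure.
2. In item 20b and the Discussion, limit the conclusion to the effect of a supervised group Tai Chi programme compared with self-directed physical activity. List expectation, attention and group contact as a limitation, naming toe and heel clearance, self-selected gait speed, single-leg stance and the Timed Up and Go as the outcomes most exposed.
3. Optionally, for anyone not yet randomised, record expected benefit before allocation is revealed and report it by arm. The Trial status section gives completion by December 2021, so this may no longer be possible; the correction does not depend on it.

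The first two items cost only wording, and the downside is a narrower claim. The third adds one baseline question.

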### Procedure for unblinding if needed {17b}

N/a.

## Data collection and management

### Plans for assessment and collection of outcomes {18a}

A 10-camera Vicon motion analysis system (two Vicon Vantage and eight Vicon Bonita optical cameras, Oxford Metrics, Oxford, UK) with a sampling rate of 200 Hz will be used to capture the participants’ gait and obstacle crossing. Prior to data collection, 45 reflective markers (14 mm diameter) will be placed on the participants’ body landmarks according to a modified Helen Hayes marker set. Ground reaction forces will be collected using four force plates recorded at 1000 Hz (two Kistler models: Kistler Instruments Corp, Winterthur, Switzerland; two Bertec models: Bertec Corporation, Columbus, OH, USA). The force plates will be embedded in the middle of an 8-m-long walkway. The participants from the TC and PA (control) groups will be required to visit the University of Ottawa’s Human Movement Biomechanics Laboratory on three laboratory sessions at baseline and at 6- and 12-week post-intervention. The data collection session will consist of preliminary screening questionnaire, gathering of anthropometric data, 3D motion capture during obstacle crossing and walking, and neuropsychological assessment of executive functioning.

#### 3-D motion capture

Gait performance test: Participants will be asked to walk along the 8-m-long walkway at their self-selected comfortable speed during which their movement will be recorded using 3D motion capture for the analysis of their 3D kinematics and kinetics characteristics of the gait. Walking performance will be used as a baseline condition for comparison with obstacle crossing, because it is a simple task to perform and can provide some indications to the participants’ overall health and functional status. Five successful walking trials will be collected.Obstacle crossing test: Participants will perform obstacle crossing in the laboratory for the analysis of their dynamic postural stability and gait performance. An obstacle composed of two upright upholders and a crossing plank with a height of 20 cm will be placed in the middle of the walkway, where the force platforms are embedded. This plank has been made easily collapsible to keep the participants safe to prevent fall. Five successful obstacle-crossing trials will be collected.

#### Neuropsychological assessment

The three following neuropsychological assessment tools were used to examine executive functioning: Trail Making Test Part B (TMT-B), Wisconsin Card Sorting Test (WCST), and Stroop Test. These three neuropsychological assessment tools are commonly used to measure executive functioning in aging research and have been recommended as a popular screening tool for the assessment of mild cognitive impairment [29, 30].TMT-B: participants will be provided with a set of numbers and letters and will be asked to connect a line from a number to a letter in ascending order. The time that it takes the participant to complete this task will be recorded.WCST: participants will be given a deck of 64 cards and will be asked to sort the cards according to shape, color, and number. The number of errors made and the number of successful sorted categories (maximum of 6) will be recorded. Participants will receive feedback about sorting the cards as “correct” or “incorrect”. After completing 10 consecutive sorts, the participants will switch to the next sorting category and this repeated until all the cards in the deck have been sorted.Stroop Test: participants will be asked to name the color but not to read the word on a card. A color-word score will be given based on the total read in 45 s.

For the 3-D motion capture, the data will be collected and analyzed using Vicon’s *Nexus* software (v. 2.8.1) and tabulated in MATLAB (v. 7.1. Release 2006a) to obtain the temporal and spatial parameters. The functional and neuropsychological assessment measures will be gathered and stored both as hard and digital copies for further data interpretation and analysis. Descriptive analysis of the movements will be first conducted. The completion of all trials will be checked, and missing trials will be checked. For the 3D motion capture data of the participants’ movement, the data will be digitized, filtered, and processed. All *Nexus* software calculations will be derived from the Plug-in-gait model (Vicon Oxford Metrics, Oxford, UK). For each trial that will be collected, the data will be normalized to one full gait cycle. One gait cycle is defined as the succession of repeated foot-strike to the next foot-strike of the same foot. The primary outcomes will be normalized by the participants’ body height and weight.

### Plans to promote participant retention and complete follow-up {18b}

Participants in the TC group will be asked to partake in three 1-h TC class per week for 12 weeks. This duration and frequency of practice have previously been used in past TC studies for this population to achieve the desired beneficial effects on postural stability and movement capacity [13, 31]. The selected intensity, duration, and frequency of the training are appropriate to meet the demands of a low-to-moderate level of exercise classification.

To mitigate any feelings of physical discomfort or muscle fatigue, we will instruct the participants to warm up prior to the training and perform each TC form at their preferred comfortable speed. The participants will be allowed to rest or take breaks when they prefer. Based on our previous conducted research in TC biomechanics and intervention, practicing TC is safe to seniors [15, 16, 18, 32]. However, a participant that feels any discomfort may withdraw from the study at any time for any reason.

The safety of the participants in the community center and laboratory settings is a primary consideration. At all times during training session or laboratory testing, both the TC instructor, PI, and/or a research assistant(s) will be present to monitor the performance and abilities of each individual participant. Participants who are deemed to be at risk of falling will be provided with a spotter, who will ensure the safety of the participant. Monitoring by the PI, instructor, and/or research assistant will help to prevent accidental trips and falls. During the TC session, the participants’ progress in the TC program will be monitored. To encourage compliance in the program, the PI will confer with the participants’ daily activity log of their TC practice to see if they are achieving the weekly goals and objectives for the class.

